### Interim analyses {21b}

An interim analysis for the trial is not planned.

### Methods for additional analyses (e.g. subgroup analyses) {20b}

No subgroup analysis has been planned, however, quality of life analysis will be conducted.

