### Objectives {7}

#### Primary objectives of the trial

Despite a wealth of in vitro and retrospective findings that clopidogrel’s anti-platelet function is severely or completely absent in patients harboring the *2 allele of the *CYP2C19* gene, a prospective clinical trial is needed. The focus of this study is on patient outcomes to unequivocally establish the benefits of treating only those patients who cannot activate clopidogrel with more costly alternatives. However, these alternatives may impose a potentially higher risk for bleeding events. Our current prospective parallel assignment trial, which is the first multicenter pharmacogenetics Randomized Controlled Trial (RCT) in the field of personalized cardiovascular medicine in the Middle East, aims to study the benefits of treating only those STEMI patients that cannot activate clopidogrel with more costly alternatives that have shown to be more effective in platelet inhibition which will lead to reduced events but with a higher bleeding risk. Therefore, the objective of this study is to assess the efficacy, complication free survival, safety and cost-effectiveness of the CYP2C19 genotype guided antiplatelet treatment strategy, using clopidogrel or prasugrel/ ticagrelor. The primary outcomes are the numbers of patients in the groups who develop an adverse major cardiovascular event within one-year post PCI, including:
Recurrent MINon-fatal strokeCardiovascular deathPLATO major bleeding

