### Trial design {8}

This is the first multicenter RCT in the field of personalized cardiovascular medicine in the Middle East and aims to prove the value of bedside pharmacogenetic testing in approximately 1500 STEMI patients undergoing PCI. This study is a prospective parallel assignment trial, the aim of which is to determine whether prescribing prasugrel or ticagrelor, rather than clopidogrel, after primary PCI in carriers of *CYP2C19**2 LoF alleles is superior in reducing a net clinical benefit outcome consisting of cardiovascular death, myocardial infarction (MI), stent thrombosis, stroke and Platelet Inhibition and Patient Outcomes (PLATO) major bleeding. All patients aged between 18 and 70 years are eligible for inclusion. The sample size calculation is based on the estimated event rates for the primary net clinical benefit endpoint. The estimated event rate of the active arm is 9%, based on the recently published Patient Outcomes after primary PCI (POPular Genetics) trial and the Saudi Acute Myocardial Infarction Registry (STARS) [15–21]. The estimated event rate for the control arm is 13.6%, based on the PLATO trial [19, 20]. Using a power of 80% and an alpha level of 0.05, 1484 patients are required. Accounting for drop-outs 1500 patients will be included. Data are entered on http://www.openclinica.nl.

ST-segment elevation MI is defined according to the European Society of Cardiology and American College of Cardiology guidelines [8]. All demographic and clinical data are obtained for each participating patient from the medical records at the time of the index PCI. The treating physicians are not blinded to group allocation since the therapy could require alteration in patients with *CYP2C19*2* LoF alleles.

The Spartan RX device is being used to determine the *2 genotype of patients. The Spartan RX *CYP2C19*2* platform is placed in the catheterization lab of each hospital to enable immediate genetic testing. The trial was conducted in accordance with SPIRIT guidelines.

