## Interventions

### Explanation for the choice of comparators {6b}

#### Active comparator: Clopidogrel

*CYP2C19* genotyping will be carried out at the end of the study period. DNA is extracted from the collected blood samples and stored at − 80 °C. Genotyping will be conducted using the Spartan RX device. Clopidogrel is being used for treatment for one year according to local protocol. Clopidogrel is the standard of care in Saudi Arabia due to wider availability and lower costs. Patients receive clopidogrel 75 mg per day.

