#### Plans for collection, laboratory evaluation and storage of biological specimens for genetic or molecular analysis in this trial/future use {33}

Blood samples and buccal swabs collected from the control arm are stored at − 80 until analysis at the end of the one-year period.

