### Statistical methods

#### Statistical methods for primary and secondary outcomes {20a}

All analyses will be carried out on an intention-to-treat basis. Binary and other categorical variables will be compared using χ^2^ test or Fisher’s exact test, as appropriate. For continuous data, two-sided unpaired student’s t tests will be used. Comparison between groups will be undertaken using Cox regression analysis. At the end of the study, cost-effectiveness and quality of life will be determined in the study groups by determining the quality-adjusted life-years, net cost per life year gained and net cost per quality-adjusted life-years. Cost-effectiveness will be estimated from societal and healthcare perspectives as described in the methods reported for pharmacoeconomic research [25]. Data will be analyzed using SPSS version 24.

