### Methods in analysis to handle protocol non-adherence and any statistical methods to handle missing data {20c}

The method of analysis is by intention to treatment (ITT) which classifies participants based on the treatment to which they were originally randomized. For sensitivity purposes, a per protocol analysis will also be performed.

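### The trial design section poses a question about carriers that no planned analysis addresses, although the control arm will be genotyped and a randomised carrier comparison could be added

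*Protocol article*

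**What the plan says.** The protocol article states its aim in two ways. Trial design {8} asks "whether prescribing prasugrel or ticagrelor, rather than clopidogrel, after primary PCI in carriers of" the \*2 loss-of-function alleles is superior on the net clinical benefit outcome. The primary objectives instead set out to assess efficacy, complication-free survival, "safety and cost-effectiveness of the CYP2C19 genotype guided antiplatelet treatment strategy", and Sample size {14} powers the trial for superiority of that strategy.

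The analyses follow the second version. Section {20a} says "All analyses will be carried out on an intention-to-treat basis", and section {20c} adds "For sensitivity purposes, a per protocol analysis will also be performed". Neither mentions a restriction to carriers. Section {20b} is explicit: "No subgroup analysis has been planned, however, quality of life analysis will be conducted".

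Genotype will nevertheless be known in both arms. Active-arm patients are typed at the bedside. For the control arm, the comparator section says "genotyping will be carried out at the end of the study period", and section {33} says "Blood samples and buccal swabs collected from the control arm are stored at" −80 until analysis. The article describes no use of the control genotype in any analysis.

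All control patients and the active-arm non-carriers are assigned clopidogrel 75 mg daily.

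**The concern.** A question posed in the design section has no analysis, and the article rules the relevant one out explicitly. This is therefore not a detail left to an analysis plan that we cannot see.

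Genotype is fixed before randomisation. Carriers in the active arm against carriers in the control arm is therefore a comparison protected by randomisation, provided that genotyping is complete and does not depend on outcome. It isolates the patients whose assigned drug differs between arms. Every planned comparison mixes them with a much larger group assigned the same drug either way.

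There are two risks. A null whole-arm result could be read as no benefit in carriers. A carrier analysis added after the results are known would contradict section {20b} and be treated as post hoc.

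**Working it through.** **Inputs from the article.** Event rates are 13.6% (control) and 9% (active), with alpha 0.05, power 80%, and 1484 patients required, raised to 1500 (Sample size {14}). Carrier prevalence is about 26% for \*2 and/or \*3 (Background) and about 20% for \*2 (Abstract, Discussion).

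**Assumptions.** Allocation is 1:1 and the test two-sided (neither is stated; together they reproduce the sample size). Prevalence in the trial equals the population figures.

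**1. The plan's own figure.** Pooled-variance formula for two proportions, mean rate 0.113:

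n = [1.96·√(2·0.113·0.887) + 0.842·√(0.136·0.864 + 0.09·0.91)]² / 0.046² ≈ 743 per arm, or 1486 in total.

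The stated 1484 is reproduced within rounding. Power at 750 per arm is 80.4%. The sample size is not an arithmetic error.

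**2. Dilution.** The share assigned clopidogrel in either arm is 1 − 0.26 = 74% or 1 − 0.20 = 80%. Carriers per arm number 0.26·750 = 195 or 0.20·750 = 150. If only carriers contribute to the planned 4.6-point difference, their absolute reduction must be 4.6/0.26 = 17.7 points or 4.6/0.20 = 23.0 points.

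**3. Power with assumed carrier risk ratios.** Let f be the prevalence, r the event rate of non-carriers, and k·r the rate of carriers on clopidogrel. Assume that carriers on the alternative drug fall to r. Holding the control arm at 13.6% gives r = 0.136/(1 − f + f·k), and the whole active arm then has rate r. The values of k are not in the documents.

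Power = Φ[(d − 1.96·SE₀)/SE₁], where d is the rate difference, SE₀ is pooled and SE₁ unpooled.

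Example with f = 0.26 and k = 2: r = 0.136/1.26 = 10.8% and k·r = 21.6%. With 195 per arm, SE₀ = 0.0373 and SE₁ = 0.0369, so power = Φ[(0.1079 − 1.96·0.0373)/0.0369] = 83%. For whole arms, 13.6% against 10.8% with 750 per arm gives 38%.

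| Prevalence | Carrier risk ratio | Carriers on clopidogrel vs alternative | Power, carriers | Power, whole arms |
|---|---|---|---|---|
| 26% | 1.5 | 18.1% vs 12.0% | 38% | 15% |
| 26% | 1.75 | 19.9% vs 11.4% | 64% | 25% |
| 26% | 2.0 | 21.6% vs 10.8% | 83% | 38% |
| 20% | 1.5 | 18.5% vs 12.4% | 32% (31.5% before rounding) | 11% |
| 20% | 1.75 | 20.7% vs 11.8% | 55% | 18% |
| 20% | 2.0 | 22.7% vs 11.3% | 75% | 26% |

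**4. Power if carriers show only the planning rates.** Suppose carriers go from 13.6% to 9% and non-carriers stay at 13.6% in both arms. The active-arm rate is then 0.26·9 + 0.74·13.6 = 12.4%, or 0.20·9 + 0.80·13.6 = 12.7%. Power in carriers is 30% (26% prevalence) or 24% (20%), against 10% or 8% for whole arms.

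**5. Power at the planning rates for whole arms.** Setting r = 9% in the model of step 3 gives k = (0.136/0.09 − 1 + f)/f, about 3.0 at 26% and 3.6 at 20%. Whole-arm power is then the planned 80%.

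**The case against.** The strongest reply is that this is a trial of a strategy. The objectives and the sample size section say so, and for that aim the whole-arm intention-to-treat comparison is the right analysis, including for cost-effectiveness. This stands. A reader might infer from Trial design {8} alone that the trial cannot answer its own aim. The documents do not support that, because one of the two stated aims is answered validly. Nor are non-carriers mere noise: they belong to the population that the strategy treats and costs.

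A reader might also infer that a single diluted comparison is all that is planned. In fact per-protocol, secondary-outcome, cost-effectiveness and quality-of-life analyses are planned too. None is described as restricted to carriers, so the dilution remains. Likewise, the secondary objective on quality of life names patients on alternative therapy, but section {20a} determines it in the study groups, so it is not confined to treated carriers.

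The power figures are open to challenge. The risk ratios are assumed. Letting treated carriers fall to the non-carrier rate is favourable for a composite that includes major bleeding, since the article itself expects more bleeding on the alternatives. At the planning rates, whole-arm power is 80% (step 5), so the low whole-arm power depends on the scenario. The carrier comparison is also underpowered in much of the range. What survives is the ranking: it has more power than the whole-arm comparison in every scenario of steps 3 and 4.

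**Conclusion.** The point holds as a gap between the stated aims and the planned analyses. The strategy question has a valid primary analysis. The carrier question in Trial design {8} has none, section {20b} excludes one, and the genotypes that it needs are already to be collected.

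Across assumed risk ratios of 1.5 to 2.0, power in carriers is about two to three times that for whole arms at either prevalence. It reaches 80% only at a ratio of 2.0 with 26% prevalence. If carriers merely go from 13.6% to 9%, neither comparison is adequate. These sizes rest on the assumptions listed above. The dilution of 74% to 80% rests only on the article's prevalence figures and assigned drugs; actual drug use may differ, because switching is left to the treating physician.

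**What to change.** - Reconcile the primary objectives, Trial design {8} and section {20b}, and keep the whole-arm intention-to-treat comparison as primary.
- Before control genotypes are linked to outcomes, prespecify in sections {20a} and {20b} a key secondary analysis: the primary composite in carriers, by randomised arm, with the same model as the primary. Show non-carriers alongside and report a genotype-by-arm interaction test.
- Fix one carrier definition for this analysis that the assay can deliver in both arms. The intervention-group sections refer to \*2 and/or \*3, whereas Trial design {8} and Intervention description {11a} refer to \*2 only. These passages must be reconciled.
- Genotype all control patients regardless of outcome, including those who died or withdrew, with the laboratory blind to outcome. State a rule for failed or missing genotypes: bedside typing in one arm and later typing in the other could leave unequal gaps.

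The cost is plan wording and a little extra analysis, since samples and control genotyping are already planned and the article reports that data analysis has not begun. The drawback is limited power in carriers if the effect is modest, so a null carrier result should not be read as evidence of no effect.

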### Methods in analysis to handle protocol non-adherence and any statistical methods to handle missing data {20c}

The method of analysis is by intention to treatment (ITT) which classifies participants based on the treatment to which they were originally randomized. For sensitivity purposes, a per protocol analysis will also be performed.

### Plans to give access to the full protocol, participant level-data and statistical code {31c}

Once the study is completed, the outcome will be published in scientific journals and coded data will be made available upon request.

### Oversight and monitoring

#### Composition of the coordinating Centre and trial steering committee {5d}

The investigators in King Fahd Hospital of the University are responsible for coordinating and managing data.

#### Composition of the data monitoring committee, its role and reporting structure {21a}

The data monitoring committee comprises [name], [name], [name], [name], and [name]. The role of this committee is to oversee data entry and data accuracy. All investigators involved in this project are independent from the sponsor, have no competing interests and report directly to the principal investigator, [name]. A member of the Department of Internal Medicine at each hospital independently audits the conduct of the trial. These auditors review documentation at the end of each six-month period and compare the documentation to the data on the clinical trial web site. In addition, the auditors determine whether documentation is complete, and if not, reports this to the principal investigator to resolve the issue.

#### Adverse event reporting and harms {22}

In the event of a patient developing side effects to the P2Y12 inhibitor, the patient would be withdrawn from the trial and it is up to the attending physician to reassign the patient to his or her original treatment plan. Any adverse event and any other unintended effect of the trial is reported immediately and directly to the data monitoring committee.

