### Criteria for discontinuing or modifying allocated interventions {11b}

Treatment with a P2Y12 inhibitor is standard care and is continued until the end of follow-up. Switching between P2Y12 inhibitors or early discontinuation is at the discretion of the treating physician. A patient is excluded from the study if he or she requests this or if the patient relocates to another region of Saudi Arabia as this prevents the patient from being followed up.

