#### Plans to promote participant retention and complete follow-up {18b}

All participants are given a leaflet which explains the objectives, rationale, and importance of participating in this trial. The treating cardiologist explains that patient confidentiality is maintained during and after the trial and addresses any concerns the potential applicant may have and that the participant can withdraw from the trial at any time. The cardiologist also emphasizes the importance of attending scheduled appointments but will facilitate rescheduling appointments to provide flexibility. Outcome data of participants who withdraw from the trial are treated as confidential and at the end of the study the investigators will contact these participants to seek permission to include their data in the study.

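### Withdrawing patients from the trial for P2Y12 side effects, and excluding those who relocate, conflicts with the stated intention-to-treat analysis and may lose outcomes informatively

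*Protocol article*

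**What the plan says.** All references are to the protocol article.

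- **Analysis.** Section {20a}: "All analyses will be carried out on an intention-to-treat basis". Section {20c} explains that this "classifies participants based on the treatment to which they were originally randomized" and keeps a per-protocol analysis for sensitivity only.
- **Side effects.** Section {22}: "In the event of a patient developing side effects to the P2Y12 inhibitor, the patient would be withdrawn from the trial". What is left is the trial, not only the drug.
- **Relocation or request.** Section {11b}: "A patient is excluded from the study if he or she requests this or if the patient relocates to another region of Saudi Arabia". The reason given for relocation is that follow-up becomes impossible.
- **Switching or stopping.** The same section {11b}: "Switching between P2Y12 inhibitors or early discontinuation is at the discretion of the treating physician". It mentions no exit from the trial.
- **Data of those who withdraw.** Section {18b}: "at the end of the study the investigators will contact these participants to seek permission to include their data in the study".
- **Endpoint and expected harm.** PLATO major bleeding is a primary component (sections {7} and {12}), and section {7} expects a higher bleeding risk with the alternatives to clopidogrel.

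**The concern.** An intention-to-treat comparison needs outcomes for everyone randomised, whatever happens to their drug. A rule that ends trial participation because of a reaction to treatment removes patients for a reason that arises after randomisation and depends on treatment. Sections {22} and {11b} also disagree: a patient who stops the drug because of a side effect leaves the trial under one and can stay under the other, so the two hospitals could apply different rules.

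The trigger overlaps the endpoint. A minor bleed could end follow-up before a later major bleed, infarction or death is recorded. Treating physicians know the allocation (section {8}) and presumably judge what counts as a side effect. Since the trial asks about net clinical benefit, harms lost from one arm would bear directly on its conclusion.

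Section {18b} offers a route back, but only at study end. Recruitment began in May 2013 and was expected to finish in December 2020, so the request could come years after withdrawal. By then, patients who have died or cannot be traced cannot give permission, and cardiovascular death is itself a primary component.

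**Working it through.** **1. The planned figures.** Inputs from section {14}: 13.6% against 9%, 80% power, alpha 0.05. Two-sided testing and 1:1 allocation are assumed, as neither is stated. With mean rate (0.136 + 0.09)/2 = 0.113 and difference 0.046:

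n per arm = [1.96·√(2·0.113·0.887) + 0.8416·√(0.136·0.864 + 0.09·0.91)]² / 0.046² = 742.4, rounded up to 743, or 1486 in total.

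This reproduces the stated 1484. The allowance for all losses is 1500 − 1484 = 16 patients (1.07%).

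**2. Who receives the stronger drugs.** The article gives carrier shares of about 20% (abstract) and 26% (background). At 750 per arm that is 150 to 195 active-arm patients.

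**3. Illustration under no true effect.** Assumptions, none of them from the protocol:
- the true rate is 11.3% in both arms (84.75 expected events per 750);
- 26% are carriers, and 10% of active-arm carriers are withdrawn;
- a share c of clopidogrel patients is withdrawn in both arms, c = 2% or 5%;
- withdrawn patients have event risk r = 30% or 50% and are dropped altogether.

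Withdrawn, active: W_A = 195·0.10 + 555·c. Withdrawn, control: W_C = 750·c. Observed rate in each arm = (84.75 − W·r)/(750 − W).

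Example, c = 2%, r = 50%: W_A = 19.5 + 11.1 = 30.6 and W_C = 15. Active: (84.75 − 15.3)/719.4 = 9.65%. Control: (84.75 − 7.5)/735 = 10.51%. Difference: 0.86 points.

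| c | r | W_A | W_C | Active | Control | Difference (points) | Type I error |
|---|---|---|---|---|---|---|---|
| 2% | 30% | 30.6 | 15 | 10.50% | 10.92% | 0.41 | 5.7% |
| 2% | 50% | 30.6 | 15 | 9.65% | 10.51% | 0.86 | 8.4% |
| 5% | 30% | 47.25 | 37.5 | 10.04% | 10.32% | 0.27 | 5.3% |
| 5% | 50% | 47.25 | 37.5 | 8.70% | 9.26% | 0.57 | 6.6% |

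Differences are taken before rounding. Type I error is the rejection probability of a two-sided 5% two-proportion z-test at the observed rates and remaining numbers. The spurious difference is 0.27/4.6 = 6% to 0.86/4.6 = 19% of the planned effect.

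**4. Sensitivity.** With 150 carriers, W_A = 15 + 600·c. The smallest case (c = 5%, r = 30%) gives 10.32% − 71.25/705 = 0.2 points; the largest (c = 2%, r = 50%) gives 10.51% − 71.25/723 = 0.7 points. If those dropped have the same risk as everyone else, the difference is zero.

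**5. Precision.** Withdrawals in step 3 total 45.6 to 84.75 patients, against the allowance of 16. Overall losses of 2%, 5% and 10% would give power of 79.6%, 78.4% and 76.2%. This matters less than the bias.

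**The case against.** **The direction is inferred.** A reader might conclude that these rules do remove events differentially from the arm given the stronger drugs. The document does not establish that. Section {22} covers side effects of any P2Y12 inhibitor, so clopidogrel patients in both arms are withdrawn too; only about 20-26% of the active arm receives the alternatives; and no side-effect or withdrawal rate is given. This objection stands, and the bias is stated here as possible only.

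**Larger figures are not supportable.** Withdrawing 5% or 10% of the active arm (37.5 or 75 patients) and none of the control arm, at 30% event risk, gives type I error of 9% or 25%. If the stronger drugs were the cause, those numbers would be 19% or 38% of 195 carriers. If they were not, control patients would be withdrawn as well and the bias would shrink. The 30-50% event risk is also an assumption.

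**Events may not be deleted.** No section says that a withdrawn patient's earlier events are discarded. Cox regression (section {20a}) can use time up to withdrawal, and a major bleed that triggers withdrawal could still count as the first event. This stands; what is then at risk is later events.

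**Section {18b} is a recovery route.** It is, but a partial one. It does not say what happens for patients who have died, or whether it covers withdrawals made by the physician. Selective loss of deaths is therefore a risk, not a stated consequence.

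**Relocation and patient request are not tied to arm.** Agreed. Leaving on request is the patient's right. For relocation the fault is exclusion in place of censoring, not evident differential bias.

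None of this removes the conflict among the sections. An analysis plan could define the analysis set more exactly, but it cannot restore outcomes that the conduct rules stop being collected.

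**Conclusion.** The contradiction is in the current text and should be corrected. Withdrawal from the trial for side effects and exclusion on relocation do not fit the promised intention-to-treat analysis, and sections {22} and {11b} disagree on trial status after a drug change. Asking permission only at study end leaves recovery of outcomes incomplete and possibly selective.

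The loss may be informative and could favour the active arm. Under the stated assumptions the spurious difference is about 0.3-0.9 points against the planned 4.6, with type I error about 5.3-8.4%. Those figures rest on assumed withdrawal rates and event risks, on 26% carriers, and on withdrawn patients being dropped outright; at equal risk the shift disappears. The conflict is documented; the size of any bias is not.

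**What to change.** Reconcile sections {11b}, {18b}, {20a}, {20c} and {22} as follows.

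1. State that a side effect, a switch or stop of the P2Y12 inhibitor, or a relocation neither ends follow-up nor removes the patient from the intention-to-treat set.
2. Obtain one-year outcomes where possible through the medical records and patient contact already described in section {18a}. Where a relocated patient cannot be followed, treat the patient as lost to follow-up and censor at last contact; do not exclude.
3. Let only withdrawal of consent end data collection. Keep events up to that date as consent permits.
4. Ask permission to use outcome data when the patient withdraws, not at study end.

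Treatment decisions stay with the physician; no position is taken on what should be given after a side effect.

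The cost is a wording amendment and some extra record checks and patient contacts, with more effort for relocated patients. The article reports recruitment as still open and analysis as not begun, so on that status the change can still be made.
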